### Inclusion criteria

Trial health centers will be recruited from OCHIN members that use CR for at least one care management or population health program that stipulates care coordination to address unmet social needs for a monthly average of ≥ 15 enrolled patients. Trial centers must also have care management staff to support programming and provide primary care.

### Data

All quantitative data will be extracted from the OCHIN EHR, including clinical-community care coordination activities performed by care management / population health providers using CR, and patients’ demographic, medical, laboratory, and social risk data.(70, 71) Qualitative data will come from periodic reflections and interviews with CM staff. Using similar methods as applied in formative activities, periodic reflections will be conducted at intervention period weeks 4 and 8. Semi-structured interviews with one key informant (e.g. care manager, health center champion) per health center will be conducted three to six months post intervention.

### Analyses

Primary outcomes will be measured at six time points for each health center: at baseline and at the end of each of the five wedge’s receipt of the intervention during the CRT. At each time point, all active CM patients receiving care management in a CR program that incorporates social risk activities (e.g. CalAIM, CCM) will be included. The analyses use an open cohort design, as some patients will be measured across multiple time points and others only once. We will identify whether each eligible patient has been screened. We will also identify if patients who screened positive for a social need were referred to a community organization; to the extent possible we will also identify which patients with social needs declined offered referrals. Currently, there is large variability in whether health centers collect data on patients who decline referrals. We will guide on collecting this information as part of implementation support, and we will investigate if we can assess declined referrals as part of our analyses. As the main outcomes are binary and patients are nested in health centers, we will use generalized linear mixed models with a binomial distribution and a logit link and include a random effect for the health center. Patient-level covariates will include age, race/ethnicity, gender, federal poverty level, insurance type, care management program (e.g. CCM; CalAIM), and a health center-level indicator of treatment arm (intervention or control) for each time point.

The analysis for closed-loop referral (secondary outcome) will be limited to patients enrolled in CM that received a referral to a community organization for a social need. Clinical outcomes of hypertension and diabetes control will be limited to enrolled patients with hypertension and/or diabetes, respectively, and a medical visit during the measurement period.

Qualitative data collected during and after the trial will be uploaded to NVivo QRS for data management and analysis. Analysis will be conducted following an immersion-crystallization approach, which entails multiple iterations of data immersion and analytic reflection to identify patterns in the data. First, the qualitative team will meet weekly to read periodic reflections and interview transcripts to develop inductive codes. As the identification of new codes slows and the team reaches agreement on code definition and appropriate application, the team will begin coding outside of weekly meetings. Continuing to meet to discuss potential revisions to codes and their definitions, the team prepares for in-depth analysis of queried codes. Once coding is complete, code queries will be generated for further analysis. In this step, reports from the queried codes are divided among team members for immersive analysis. The team will meet weekly to share content from analytic memos, outliers in the data, and begin to identify prospective themes. During this process, the qualitative team will bring emerging themes to the larger study team for further discussion, refinement, and sense-making. This process, which further strengthens analytic validity and rigor, will occur until interpretation saturation is reached.(72, 73) Informed by the 2019 National Academies of Sciences, Engineering, and Medicine report on integrating social and medical care,(8) our analysis will focus on understanding how individual, health center, and environmental factors interact to influence care management team use of CR to screen and refer for social needs and coordinate clinical-community linkages, particularly among groups that have been economically and socially marginalized. We will highlight factors related to intervention outcomes (e.g., reach, adoption, effectiveness) and generalizability of the implementation strategies and associated adjustments across health center contexts.

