## Abstract

**Background:**

Adverse social determinants of health contribute to health inequities. Practice guidelines now recommend incorporating patient unmet social needs into patient care, and payors increasingly reimburse for screening and providing related referrals to community organizations. Emergent electronic health record (EHR)-based tools can enable clinical-community linkages, but their adoption commonly faces workflow and infrastructure barriers. Targeted implementation support such as training, championship, practice facilitation, and audit and feedback, can enhance such tools’ adoption, but no prior research has assessed such strategies’ impact on the adoption of ‘enabling technologies’ supporting clinical-community linkages. This study will test whether providing targeted implementation support to safety-net primary care health center care management teams improves the sustained adoption of EHR-based enabling technologies used to 1) screen for social needs and 2) link patients to community organizations.

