Evidence from the implementation of other care management programs(29–33) and health information technologies (HIT)(34, 35) may inform operationalizing the adoption of such enabling technologies. Evidence-based implementation strategies shown to advance the adoption of other technologies in health centers include leadership support,(36) staff training,(37–40) local champions,(41–45) practice facilitation,(46) and audit and feedback.(29–33) Applying these strategies effectively requires consideration of the specific needs and context of different health centers as well as barriers specific to the adoption of enabling technologies to support clinical-community linkages.(29–32, 47, 48) It is critical to engage health center users as partners to guide the development of a set of evidence-based implementation strategies to address such barriers. A structured approach to interactively fine-tuning implementation strategies is needed to develop an implementation support intervention that can then be formally tested to generate evidence for replication across health centers.

This paper describes the protocol for a National Institutes of Health (NIH)-funded study called DEDICATE: Advancing Care Management Adoption in Community Health Centers (R01NR021115). The study will develop and evaluate the effectiveness of implementation strategies designed to support care management teams’ sustained use of EHR-based functionalities that support clinical-community linkages. It will test the hypothesis that health center partners’-adapted implementation strategies applied to enabling technologies will improve the adoption of these technologies and thus social risk screening, community referrals, and receipt of services by patients with unmet social needs. The study’s overarching goal is to improve clinical-community linkages through care management and care coordination programs that serve high-risk patients with complex health and/or social needs.

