### Main Trial Study Design

Following the formative intervention development described above, a stepped-wedge cluster randomized trial (SW-CRT) will be conducted across 20 OCHIN member health centers, with health centers serving as the clusters. A CONSORT flow diagram outlining the randomization and intervention allocation is provided in Fig. 2.(65) In this trial, the CM teams within each health center will undergo a 12-week implementation support intervention. The stepped-wedge design enables the phased delivery of the intervention to small groups of health centers (four per wedge; five wedges). This approach optimizes study resources while maintaining methodological rigor, leveraging the higher statistical power in this design compared to other CRT designs.(50, 66–68) It also ensures that all participating health centers eventually receive the intervention, potentially enhancing study recruitment.

The 20 recruited health centers will be randomly assigned to one of five wedges using a random number generator independently by the study’s statistician with SAS software for staggered receipt of the intervention. The statistician will have no direct interaction with the health centers and will not be involved in the recruitment of these health centers into the study. Recruitment efforts will be led by the study’s Project Manager and Project Director. These health centers will initially start in the control condition, with each wedge sequentially transitioning (per randomization) to the intervention condition every three months. This process continues until all health centers receive the full 12-week intervention (Table 3). Before receiving the intervention, all study health centers will contribute at least six months of baseline data. After receiving the intervention, all study health centers will continue to be followed until the end of the main trial period, which will span from approximately January 2025 (start of baseline data collection) to June 2027 (end of follow-up for all wedges). The intervention will be delivered to health centers from July 2025 to September 2026. The final wedge to receive the implementation support will be followed for six months in the intervention condition. Participating health centers will receive an impact payment for their involvement.

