**Table 3 T3:** Stepped-wedge design

					Year 1	Year 2		Year 3				Year 4				Year 5			
Q1	Q2	Q3	Q4	Q1	Q2	Q3	Q4	Q1	Q2	Q3	Q4	Q1	Q2	Q3	Q4	Q1	Q2	Q3	Q4
Wedge 1 (Health Centers 1–4)					Formative Intervention Refinement	C	C	I	F	F	F	F	F	F	Analysis and Dissemination				
Wedge 2 (Health Centers 5–8)						C	C	C	I	F	F	F	F	F					
Wedge 3 (Health Centers 9–12)						C	C	C	C	I	F	F	F	F					
Wedge 4 (Health Centers 13–16)						C	C	C	C	C	I	F	F	F					
Wedge 5 (Health Centers 17–20)						C	C	C	C	C	C	I	F	F					

Note: C = Control condition, I = Intervention condition, F = Follow-up.

**Table 4 T4:** Outcomes Per RE-AIM Framework.

RE-AIM Outcome	Outcome Type	Measure
Reach	Primary	binary outcome of whether the patient has been screened for unmet social needs
Effectiveness	Primary Secondary Secondary	binary outcome of whether the patient with an unmet social need received a referral to a community organization to address an identified social need binary outcome of controlled hypertension binary outcome of controlled diabetes
Adoption	Secondary	binary outcome of receipt of community services (closed-loop referral) among patients with a social need who were referred to community organizations
Implementation	Secondary	*assessed through qualitative methods
Maintenance	Secondary	*assessed through qualitative methods

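### The aim is sustained adoption, but the primary-outcome analysis ends with wedge 5's support, pools support and post-support quarters in one indicator, and specifies no quantitative estimate of a lasting effect

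*Protocol article*

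**What the plan says.** The Abstract states the question as whether targeted support "improves the sustained adoption of EHR-based enabling technologies", and the Background repeats it as "sustained use of EHR-based functionalities that support clinical-community linkages". The support lasts 12 weeks and is delivered from July 2025 to September 2026.

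On measurement, the Analyses section says: "Primary outcomes will be measured at six time points for each health center: at baseline" and when each of the five wedges completes its support. The treatment term is one health-center-level indicator, intervention or control, at each time point. The only random effect named is one for health center.

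Table 3 has three states: control (C), intervention (I) and follow-up (F). Every wedge has at least two F quarters. Main Trial Study Design adds: "The final wedge to receive the implementation support will be followed for six months in the intervention condition". The same section gives the end of the trial as "June 2027 (end of follow-up for all wedges".

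In Table 4, Maintenance is "assessed through qualitative methods". The Data section describes the post-support qualitative data as one key-informant interview per center, three to six months after the intervention.

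**The concern.** The support is temporary, so the question of interest is what remains once it stops. Three choices in the article work against answering it with numbers:

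- Primary-outcome measurement stops when the last wedge's support stops, although later follow-up is planned.
- Table 3 separates I from F, but the model's indicator does not.
- The RE-AIM dimension that corresponds to sustained use has no quantitative measure.

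At stake is how a positive primary result is read. As specified, it would not distinguish adoption that lasts from adoption that fades once training, coaching and feedback end.

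**Working it through.** **1. What is measured and when.** Count the quarters in Table 3, with the six time points taken as baseline plus the end of each wedge's support.

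- F quarters by wedge: 6 + 5 + 4 + 3 + 2 = 20.
- F quarters up to the end of wedge 5's support: 4 + 3 + 2 + 1 + 0 = 10. The other 10 are unused for the primary outcomes.
- Treated center-periods in the six-point analysis, by time since support ended (0, 3, 6, 9, 12 months): 20, 16, 12, 8, 4, in total 60. Of these, 60 − 20 = 40 are post-support. Wedge 5 contributes none of the 40.
- Nine quarters from January 2025 end in March 2027, which is also September 2026 plus six months. The text says June 2027.

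**2. The protocol's power reproduces.** Inputs from Sample Size Calculation: 20 centers, five wedges of four, 163 patients (taken here as per center-period), cluster autocorrelation (CAC) 0, individual autocorrelation 0, two-sided α = 0.05. I used a linear risk-difference model with period effects.

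With CAC 0, the variance of a center-period mean is v = τ² + σ²/163, with σ² = p̄(1 − p̄) and τ² = σ² × ICC/(1 − ICC). Each period contributes information (treated × control)/20. For 4/16, 8/12, 12/8 and 16/4 centers this is 3.2 + 4.8 + 4.8 + 3.2 = 16. The first and last periods contribute nothing.

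- 48% to 63.3%, ICC 0.15: σ² = 0.5565 × 0.4435 = 0.2468; τ² = 0.0436; v = 0.0451; SE = √(0.0451/16) = 0.0531; power = Φ(0.153/0.0531 − 1.96) = 82%.
- 48% to 72%, ICC 0.30: σ² = 0.24; τ² = 0.1029; v = 0.1043; SE = 0.0808; power = Φ(0.24/0.0808 − 1.96) = 84%.

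Both agree with the stated > 80%.

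**3. What the single indicator estimates if the effect changes over time.** Its expectation is a weighted sum of the effects at each time since support ended.

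- *Period effects, CAC 0.* The four informative periods have shares 3.2/16, 4.8/16, 4.8/16 and 3.2/16, that is 0.2, 0.3, 0.3 and 0.2. Each share is split equally over the wedges already treated. The support quarter receives 0.2 + 0.15 + 0.1 + 0.05 = 0.50.
- *Random intercept, no period effects.* A center with k of 6 points treated gives each treated point a relative weight of (6 − k)/6. The support quarter receives (5 + 4 + 3 + 2 + 1)/35 = 0.43.
- *Period effects, CAC 0.8 or 1.* Weights come from the same generalized least squares algebra, solved numerically.

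| Model | 0 mo | 3 mo | 6 mo | 9 mo | 12 mo |
|---|---|---|---|---|---|
| Random intercept, no period effects | 0.43 | 0.29 | 0.17 | 0.09 | 0.03 |
| Period effects, CAC 0 | 0.50 | 0.30 | 0.15 | 0.05 | 0.00 |
| Period effects, CAC 0.8 (ICC 0.15) | 0.83 | 0.37 | 0.05 | −0.12 | −0.13 |
| Period effects, CAC 1 (ICC 0.15) | 0.85 | 0.37 | 0.04 | −0.13 | −0.14 |

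*Assumed scenario A: the effect is zero once support ends.* The estimate is the first column: 43%, 50%, or 82% to 85% of the support-quarter effect (CAC 0.8 to 1, ICC 0.05 to 0.15).

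*Assumed scenario B: the effect fades 15, 10, 5, 0, 0 points.* The equal-weight average is 30/5 = 6. Weighted by observed center-periods it is (20 × 15 + 16 × 10 + 12 × 5)/60 = 8.7. The estimates are:

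- no period effects: 0.428 × 15 + 0.286 × 10 + 0.172 × 5 = 10.1;
- period effects, CAC 0: 7.5 + 3 + 0.75 = 11.3;
- period effects, CAC 0.8 to 1: about 16 to 17.

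**4. Power of a sustained-effect estimate** (first figure 48% to 63.3% at ICC 0.15; second 48% to 72% at ICC 0.30).

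| Estimate | CAC 0, 6 points | CAC 0, 8 points | CAC 0.8, 6 points | CAC 0.8, 8 points |
|---|---|---|---|---|
| Separate post-support effect | 70%, 73% | 70%, 73% | 95%, 97% | 98%, 99% |
| Time average of exposure-time effects | 69%, 72% | 64%, 67% | 85%, 89% | 71%, 76% |

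The 8-point time average covers seven exposure times rather than five. For the on/off effect, nine quarters instead of six time points leave the variance unchanged at CAC 0 (ratio 1.00) and lower it by about 13% to 18% at CAC 0.5 to 0.8.

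**The case against.** The strongest reply is that post-support data are not missing: two thirds of the treated center-periods come after support has ended. A reader might infer that the trial cannot answer its own question. The documents do not support that, because a sustained effect can be estimated from wedges 1 to 4. What is missing is a specified estimate of it.

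A reader might also infer that the last quarters enter no quantitative analysis at all. The six time points are fixed for the primary outcomes only. The timing of closed-loop referral and of hypertension and diabetes control is not given, and the later quarters may serve them.

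A third tempting reading is that the on/off estimate will lie outside the range of the true effects. In scenario B that happens only with period effects, which the article's covariate list does not name, together with substantial CAC, whereas the power calculation assumes 0. Under the other two models the estimate stays within the range, though above both averages.

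It is also fair that the Background hypothesis and the primary outcomes carry no durability condition, that the text itself describes wedge 5's follow-up as being in the intervention condition, and that qualitative Maintenance is a declared design choice. These points defend the on/off effect as the primary test. They do not supply a number for an aim that is twice worded as sustained. An unseen analysis plan may hold exposure-time analyses, but the measurement times, the treatment term and the Maintenance measure are fixed in this article. The trial span is qualified as approximate, so the date mismatch is minor.

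**Conclusion.** The point holds in a limited form. The primary-outcome schedule omits half of the planned follow-up wedge-quarters, the one treatment term merges support with post-support time, and no quantitative sustained effect is specified although the data could provide one. A positive on/off result would therefore be compatible with an effect that ended with support: in that assumed case the estimate would still be about 43%, 50%, or 82% to 85% of the support-quarter effect.

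The fading patterns are assumptions, the projections are linear approximations to the planned logit model, and 163 is read as patients per center-period. The size depends strongly on period effects and CAC; the direction in both fading scenarios does not. The primary test need not be replaced, but the plan should be amended before analysis.

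**What to change.** - Keep the on/off effect as the powered primary test.
- Extend primary-outcome measurement to every follow-up quarter in Table 3.
- With period effects in the model, prespecify a support-quarter versus post-support contrast as a key secondary analysis. Exposure-time effects with their time average are an alternative, but the power table favors the two-state contrast once the extra quarters are included.
- Add to Table 4, beside the qualitative measure, a quantitative Maintenance outcome: screening and referral 3 to 6 months after support ends.
- Reconcile the end of follow-up between Table 3 (March 2027) and Main Trial Study Design (June 2027).

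The cost is mainly wording, since the quantitative data already come from the shared EHR. The statistical cost is precision. At the protocol's CAC of 0, the sustained-effect estimate on the six time points has about 69% to 73% power, against 82% to 84% for the on/off effect, which is why it should stand beside the primary test. The extra quarters improve precision only if CAC is above 0.

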### Sample Size Calculation

We assessed power (66, 74–76) to detect differences in the percentage of patients with social needs who are referred to community organizations, which is a primary outcome of this study. We used a two-sided significance test with *α* = 0.05. The study’s pre-specified total sample size is 20 health centers with a stepped-wedge open cohort design(77) with five wedges each of four health centers (clusters). Based on preliminary data of high-acuity patients (defined as three or more chronic diseases on the Multimorbidity Weighted index(78–80)) and a completed social risk screen, the expected number of eligible patients is 163 per health center. This number represents the denominator for the primary outcome and the number of patients in each cluster. The proportion of patients with social needs who are referred to services (i.e., the numerator) varies widely, ranging from 10%(81) to 86% in the literature.(24) Therefore, we assume a baseline referral rate of 48%, which is the midpoint between the ranges. We also assume that the intervention would improve clinical-community linkages to between 63.3%(82) and 72%(23) based on other studies. To determine the power of this trial, we examined the absolute differences in screening rates for a range of intraclass correlations, which quantifies the degree of similarity in outcomes within each cluster (health center). We conservatively assumed a cluster autocorrelation and the individual autocorrelation of 0, as there are no sufficient data-driven estimates of these measures,(83) and a block exchangeable decay structure. The cluster autocorrelation refers to the correlation between the population means from the same group at two different periods, while the individual autocorrelation is the correlation between the outcome variable for the same individual at two different periods.(84) If the intervention improves screening rates to 63.3%, as observed in Lian et al. then we would have > 80% power to detect this difference with an intraclass correlation as high as 0.15. If the intervention improves screening rates to 72% as observed in Richman et. al, we would have > 80% to detect this difference with an intraclass correlation as high as 0.30. Power was calculated using the Shiny app(85) for the swCRTdesign(86) package in R.

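### The stated primary model implies a cluster autocorrelation of 1, while power was computed at 0; its standard errors are too small if center rates vary between periods

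*Protocol article*

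**What the plan says.** Protocol article, Analyses: "we will use generalized linear mixed models with a binomial distribution and a logit link and include a random effect for the health center". The reason given is that outcomes are binary and patients are nested in centers. The section describes an open cohort in which "some patients will be measured across multiple time points and others only once", and states: "Primary outcomes will be measured at six time points for each health center". It names no center-by-period term.

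Protocol article, Sample Size Calculation: "We conservatively assumed a cluster autocorrelation and the individual autocorrelation of 0", because data-driven estimates were lacking, together with a block exchangeable structure. The section defines cluster autocorrelation as the between-period correlation of population means from the same group. It claims power above 80% for 48% versus 63.3% at an ICC up to 0.15, and for 48% versus 72% at an ICC up to 0.30.

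**The concern.** With one center intercept, two patients of the same center are equally correlated (on the model scale) whether they are measured in the same period or at the first and last time points. That is a cluster autocorrelation (CAC) of 1. The power section takes the opposite extreme. The two sections therefore describe different data, and the analysis uses the structure that understates uncertainty whenever center rates move between periods.

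Such movement is plausible here. The Setting section says the tool became available in 2022 and that under 10% of centers are estimated to use its referral and tracking functions. The Limitations section names staffing, funding and community capacity as influences the design does not directly address. In a stepped wedge the treatment effect rests largely on comparing a center with itself over time, so unmodeled movement of this kind goes straight into the treatment contrast. The nominal 5% level of the primary tests is at stake.

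**Working it through.** **Inputs from the protocol.** 20 centers in five wedges of four; six time points (T = 6); two-sided alpha 0.05; control rate 48%; intervention rates 63.3% and 72%; ICC (ρ) 0.15 and 0.30; CAC 0. On cluster size, "the expected number of eligible patients is 163 per health center" does not say whether this is per period, so both m = 163 and m = 163/6 ≈ 27 are used. CAC values other than 0 and ICC 0.05 are assumptions of this review.

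**Step 1: reproduce the stated power.** At CAC 0 the center-period means are independent, each with variance v = p(1−p)[ρ + (1−ρ)/m]. With period effects fitted and treated shares 0, 0.2, 0.4, 0.6, 0.8 and 1, the variance of the effect is v / [20 × (0 + 0.16 + 0.24 + 0.24 + 0.16 + 0)] = v/16.

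- ICC 0.15: v = 0.2496 × (0.15 + 0.85/163) = 0.0387; SE = √(0.0387/16) = 0.0492; power = Φ(0.153/0.0492 − 1.96) = 87.5%.
- ICC 0.30: v = 0.2496 × (0.30 + 0.70/163) = 0.0760; SE = 0.0689; power = Φ(0.24/0.0689 − 1.96) = 93.6%.

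Taking p(1−p) at the mean rate, or averaged over arms, raises these to at most 88.6% and 95.6%. The claim of more than 80% reproduces, but for a model that carries center-by-period variance.

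**Step 2: what the stated model reports.** Set total variance to 1. The patient-level part is e = 1−ρ and the center-by-period part is b = ρ(1−CAC). A center-intercept-only fit pools b into its residual:

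s² = [T(m−1)e + (T−1)(e + mb)] / [T(m−1) + (T−1)].

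The true variance of a within-center contrast scales with e + mb, while the model uses s². Hence true SE / model SE ≈ √[(e + mb)/s²], and type I error = 2Φ(−1.96/ratio). Example at CAC 0.8, m = 163: e + mb = 0.85 + 163 × 0.03 = 5.74; s² = (972 × 0.85 + 5 × 5.74)/977 = 0.875; ratio = 2.56; type I error 44%.

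Results at ICC 0.15, with the full matrix (sandwich) calculation alongside:

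| m | CAC | e + mb | s² | Ratio | Type I error | Full calculation: ratio, type I error |
|---|---|---|---|---|---|---|
| 163 | 0 | 25.30 | 0.975 | 5.09 | 70% | 5.03, 70% |
| 163 | 0.8 | 5.74 | 0.875 | 2.56 | 44% | 2.56, 44% |
| 163 | 0.95 | 2.07 | 0.856 | 1.56 | 21% | 1.55, 21% |
| 163 | 1 | 0.85 | 0.850 | 1.00 | 5% | 1.00, 5% |
| 27 | 0 | 4.90 | 0.976 | 2.24 | 38% | 2.13, 36% |
| 27 | 0.8 | 1.66 | 0.875 | 1.38 | 15% | 1.37, 15% |
| 27 | 0.95 | 1.05 | 0.856 | 1.11 | 8% | 1.11, 8% |

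Other ways of setting the fitted variance components move these by up to about three points. At a smaller ICC of 0.05, with CAC 0.8 and m = 163, the formula gives a ratio of √(2.58/0.958) = 1.64 and 23% (simulated 17%).

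**Step 3: simulated logit mixed models.** No true effect, center intercept and period effects fitted, ICC 0.15, m = 163, in two independent runs of 200 and 150 replicates:

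- CAC 0: rejection 64% and 66%; empirical SD of the estimate 0.225 and 0.213 against a mean model SE of 0.051 in both.
- CAC 0.8: 36% and 39%.
- CAC 1: 3.5% and 6%, so the procedure is near nominal when the model is right.

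**Step 4: repeated patients.** At CAC 1 with patient correlation ignored and period effects fitted, true SE / model SE is 0.71 for a closed cohort with individual autocorrelation 0.5, and 0.80-0.95 for assumed open cohorts. At CAC 0 (ICC 0.15, m = 163), adding patient correlation leaves the ratio at about 5.0.

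**The case against.** The article is condensed. It says the models include a center effect and does not exclude further terms, and an unseen analysis plan may add them. That stands as a limit: the final model is not known to lack a center-by-period term. It does not remove the point, because the article states one random-effects structure for analysis and an incompatible one for power.

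CAC 0 was chosen as a pessimistic bound and 0.15 is the top of an ICC range, so a reader who takes 64-70% as the expected error rate goes further than the documents allow. It is a worst case that also reads 163 as per period. The 163 is given for the referral outcome only; no screening denominator is stated, so the size for that outcome is not established.

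A reader might also infer that measuring patients repeatedly makes the standard errors too small. Step 4 shows the reverse: ignoring patient correlation leaves them about right or too large. Nor is a further small-sample error from Wald tests with 20 clusters supported: rejection at CAC 1 was near nominal, and the article names no test or degrees-of-freedom method.

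Finally, the calculations fit period effects, which the article's covariate list does not name. In the linear calculation leaving them out barely changes the ratio (2.20 against 2.13 at m = 27, ICC 0.15, CAC 0).

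**Conclusion.** The inconsistency is real and should be corrected before analysis. As stated, the primary model is valid only if center rates do not vary between periods beyond the common trend, which the protocol neither claims nor has data to support. The size is conditional on CAC and on patients per center-period. At ICC 0.15 and 163 per period, type I error runs from nominal at CAC 1 through about 21% at 0.95 and about 45% at 0.8 (simulated 36-39%) to about 70% at 0 (simulated 64-66%). At about 27 per period it is about 8%, 15-16% and 36-39% at CAC 0.95, 0.8 and 0. These figures rest on a linear approximation with fitted period effects, supported by the logit simulations at CAC 0, 0.8 and 1 for 163 per period. The missing center-by-period term drives the inflation; repeated patients and Wald tests do not.

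**What to change.** Add a health-center-by-period random effect to the primary mixed model, alongside the center random effect and fixed period effects, so that the analysis matches the block exchangeable structure used for power. A patient random effect is reasonable for an open cohort, though not because its omission shrinks the standard errors. Small-sample degrees of freedom or a permutation test over wedge assignment are optional sensitivity analyses. State also whether 163 is per period or in total.

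The cost is one model term, some computing, and wider but valid intervals. At CAC 0 and 163 per period, power is 87.5-88.6% (ICC 0.15) and 93.6-95.6% (ICC 0.30); with p(1−p) read as within-cluster variance it is 81.8-83.1% and 83.0-86.6%. If 163 is the total over six periods, it is 82.0-83.4% and 92.0-94.3%; with the within-cluster reading as well, it is 75.6-77.0% at ICC 0.15 and 80.4-84.2% at ICC 0.30. Only the 75.6-77.0% case falls short of the stated 80%.
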